## Abstract

**Background:**

Current first-line standard of therapy for metastatic urothelial carcinoma is platinum-based combination chemotherapy. Pembrolizumab in phase III has demonstrated a promising overall response rate of 21.1% in patients with progression or recurrence after platinum-based chemotherapy. Preclinical and clinical evidence suggests that radiotherapy has a systemic anti-cancer immune effect and can increase the level of PD-L1 and tumor infiltrating lymphocytes in the tumor microenvironment. These findings gave rise to the hypothesis that the combination of radiotherapy with anti-PD1 treatment could lead to a synergistic effect, hereby enhancing response rates.

**Methods:**

The phase I part will assess the dose limiting toxicity of the combination treatment of stereotactic body radiotherapy (SBRT) with four cycles of pembrolizumab (200 mg intravenously, every 3 weeks) in patients with metastatic urothelial carcinoma. The dose of both pembrolizumab and SBRT will be fixed, yet the patients will be randomized to receive SBRT either before the first cycle of pembrolizumab or before the third cycle of pembrolizumab. SBRT will be delivered (24 Gy in 3 fractions every other day) to the largest metastatic lesion. Secondary objectives include response rate according to RECIST v1.1 and immune related response criteria, progression-free survival and overall survival. The systemic immune effect triggered by the combination therapy will be monitored on various time points during the trial. The PD-L1/TIL status of the tumors will be analyzed via immunohistochemistry and response rates in the subgroups will be analyzed separately. A Simon’s two-stage optimum design is used to select the treatment arm associated with the best response rate and with acceptable toxicity to proceed to the phase II trial. In this phase, 13 additional patients will be accrued to receive study treatment.

**Discussion:**

The progress made in the field of immunotherapy has lead to promising breakthroughs in various solid malignancies. Unfortunately, the majority of patients do not respond. The current trial will shed light on the toxicity and potential anti-tumor activity of the combination of radiotherapy with anti-PD1 treatment and may identify potential new markers for response and resistance to therapy. *Trial registration* this trial is registered on clinicaltrials.gov (NCT02826564).

**Electronic supplementary material:**

The online version of this article (doi:10.1186/s12967-017-1251-3) contains supplementary material, which is available to authorized users.

## Background

Metastatic urothelial carcinoma remains a disease that is associated with few therapeutic options, poor prognosis and short-term survival. Worldwide, an estimated 429,800 of new cases of urinary bladder cancer and 165,100 deaths occurred in 2012 [1].

Cisplatin-containing combination therapy is standard-of-care for metastatic patients, with a median overall survival (OS) of 12.5–15 months and a long-term disease free survival in about 15% of patients [2–5]. Unfortunately, approximately 50% of patients are unfit for cisplatin-containing chemotherapy and may only be palliated with carboplatin-based regimens, without a statistically significant improvement in OS or progression-free survival (PFS) [2, 6].

Therapies blocking the PD-1/PD-L1 pathway (e.g. pembrolizumab, nivolumab and atezolizumab) have shown encouraging responses in patients with metastatic urothelial carcinoma, with an overall response rate of 15–26% [6–10]. This has resulted in the recent FDA approval of nivolumab and atezolizumab for the treatment of patients with locally advanced or metastatic urothelial carcinoma whose disease has worsened during or following platinum-containing chemotherapy, or within 12 months of receiving platinum-containing chemotherapy, either before (neoadjuvant) or after (adjuvant) surgical treatment. Patients responding to anti-PD-1/PD-L1 therapy often have tumors with elevated PD-1 and PD-L1 expression and are infiltrated by CD8+ cytotoxic tumor infiltrating lymphocytes (TIL) [8, 9, 11, 12]. These tumors are referred to as PD-L1+ TIL+.

Unfortunately, a substantial number of patients do not respond to anti-PD-1/PD-L1 therapy, often patients with low levels of tumor-infiltrating CD8+ T cells and no signs of T cell activation [12, 13]. These tumors are referred to as PD-L1− TIL−. It is hypothesized that in these non-responding patients, the tumor microenvironment might hinder T cell infiltration and induction of local endogenous immune responses.

Radiotherapy might increase response rates by creating a more permissive tumor microenvironment through increasing PD-L1 expression on tumor cells [14] and stimulating the accumulation and activation of CD8+ T cells [15], all markers for response. Preclinical evidence clearly indicates that combining radiotherapy with anti-PD-1 treatment increases the anti-tumoral activity of both treatments and even produces long-term survival [16]. On the one hand, radiotherapy might stimulate the induction of local endogenous immune responses by anti-PD-1 treatment. On the other hand, active immune stimulation by anti-PD-1 treatment within the tumor microenvironment might maximize radiation-induced antitumor immunity. These positive effects of radiotherapy are most often observed using high-dose per fraction radiotherapy (>5 Gy per fraction), which can be delivered safely in patients using stereotactic body radiotherapy (SBRT) [17–19].

Both anti-PD-1 treatment as well as SBRT (3 × 8 Gy) have shown to be safe when applied separately with grade 3–5 treatment related adverse events in 15% [10] and 11,7% [20] of patients respectively. Before the combination of drugs can be implemented in routine practice, the safety has to be established in a phase I trial as SBRT might increase the toxicity of anti-PD-1 treatment or the other way around. In addition, the timing of SBRT might influence the induction of antitumor immunity; yet this has not been thoroughly investigated [21]. Consequently, patients will be randomized into two arms with different timing of SBRT.

This trial uses a parallel phase I/II clinical trial design for combination therapies [22]. This design allows assessment of the safety and the efficacy of a combination therapy (pembrolizumab and SBRT) in a relatively small number of patients [22].

## Methods/design

### Objectives

The primary objective of the phase I trial is to evaluate the safety of the combination treatment and determine the SBRT-schedule associated with dose limiting toxicity (DLT) in <20% of patients.

The secondary objectives of the phase I trial are to assess the response rate according to the response evaluation criteria (RECIST) v1.1 and the immune related response criteria (irRC), local control, progression-free survival and overall survival. Exploratory endpoints include systemic immunologic responses and response rates in PD-L1− TIL− tumors.

### Trial design

This trial uses a parallel phase I/II clinical trial design for combination therapies [22]. Pembrolizumab (200 mg, intravenously) will be administered every 3 weeks until disease progression or unacceptable toxicity. Patients will be randomized to receive SBRT either before the first cycle of pembrolizumab or before the third cycle of pembrolizumab. SBRT will be delivered (24 Gy in 3 fractions every other day) to the largest metastatic lesion that can be irradiated safely; the last fraction will be administered 1 day prior to the subsequent cycle of pembrolizumab. Figure 1 shows a general scheme of the trial design. A more detailed table of the trial enrolment, interventions and assessments can be found in the Additional file 1: Table S1.

**Fig. 1 Fig1:**
[figure not shown]
General scheme of the trial design

### Outcome measures

#### Primary endpoint

DLT occurring between the start of SBRT and 12 weeks after completion of SBRT. DLT will be assessed using the Common Terminology Criteria for Adverse Events (CTCAE) version 4.0. DLT should be, completely or in part, related to trial therapy. The following events will be considered as DLT: any grade 3–5 metabolic or hematological toxicity that is related, probably related or possibly related to pembrolizumab or SBRT.any grade 3–5 non-hematological toxicity that is related, probably related or possibly related to SBRT.

#### Secondary endpoints

Objective response rate in the non-irradiated metastases as determined by RECIST v1.1 [23]. Response rate will be defined as the percentage of subjects achieving either a complete or a partial response at 12 weeks after the start of pembrolizumab. During treatment all patients will undergo a CT of the chest, abdomen and pelvis every 9 weeks or sooner if clinically indicated.Objective response rate in the non-irradiated metastases as determined by irRC [24] at 12 weeks after the start of pembrolizumab.Local control defined as the time between local irradiation and the moment the irradiated lesion shows an increase in size of ≥20%, according to the RECIST v1.1, confirmed by a consecutive assessment at least 4 weeks after first documentation.PFS defined as the time from inclusion to documented disease progression according to irRC or death from any cause.OS defined as the time from inclusion to death from any cause.

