### Sample size

In the first phase of the trial 20 patients will be recruited and randomly assigned to a treatment arm. If the chance that the posterior toxicity probability rate exceeds 0.2 is more than 0.7 in a certain arm, this arm will be closed.

The secondary endpoint is the assessment of the response rate of the combination treatment in non-irradiated metastases in every arm. For this analysis a Simon’s two-stage optimum design will be used [29]. The arm with the best response rate and with acceptable toxicity will be used to proceed into the second phase. The null hypothesis that the true response rate is 0.21 [10] will be tested against a one-sided alternative. If there are two or fewer responses, the alternative hypothesis will be rejected. Otherwise 13 additional patients will be accrued for a phase II trial. The null hypothesis will be rejected if 7 or more responses are observed in 23 patients. This design yields a type I error rate of 0.15 and power of 0.8 when the true response rate is 0.41 (Table 2). We consider the chance that both arms in phase 1 are deemed safe with equal toxicity and equal response rates very small. Since both arms will then qualify to continue to phase 2, selection of one arm will depend on secondary outcomes available at that time (e.g. PFS, OS).

**Table 2 Tab2:** Simon’s two-stage optimum design

Optimal two stage design	Optimum design
First stage sample size (n1)	10
r1	2
Maximum sample size (n)	23
r2	6

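### Once an arm has passed the first-stage rule, the plain percentage of 23 patients overstates response by about 2 to 6 points on average; the 13 second-stage patients should be shown beside it

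*Protocol article*

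**What the plan says.** Under Secondary endpoints the protocol article defines the measure: "Response rate will be defined as the percentage of subjects achieving either a complete or a partial response at 12 weeks". The interval is counted from when pembrolizumab begins, and only the non-irradiated metastases are assessed.

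The Sample size section sets the two-stage rule. Table 2 gives 10 patients in the first stage, with r1 = 2, n = 23 and r2 = 6. On the first-stage result it says: "If there are two or fewer responses, the alternative hypothesis will be rejected". It goes on: "Otherwise 13 additional patients will be accrued for a phase II trial". The final rule pools both stages: "The null hypothesis will be rejected if 7 or more responses are observed in 23 patients". The Data analysis section repeats that rule. The benchmark is external: "The null hypothesis that the true response rate is 0.21 [10] will be tested against a one-sided alternative".

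The arm that goes forward is the one with the better response rate and acceptable toxicity. The article names no estimate that allows for the first-stage rule. The analysis plan is not shown.

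**The concern.** A 23-patient response rate exists only when the first 10 patients supplied 3 or more responses. Keeping those 10 in numerator and denominator carries that requirement into the percentage. Had they given 2 or fewer, there would be no 23-patient figure to report.

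The phase II arm has no concurrent control, so its percentage will be read against 0.21. The planned improvement is 0.41 − 0.21 = 20 points. If conditioning on continuation alone supplies several of those points, a follow-on trial planned from the figure would start from too favourable a rate.

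**Working it through.** **Inputs** (Sample size section and Table 2): first stage 10, continue at 3 or more; second stage 13; success at 7 or more of 23; p0 = 0.21, p1 = 0.41. Let X1 ~ Bin(10, p) and X2 ~ Bin(13, p) be independent.

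**The plan's own figures.** The probability of success is the sum over x1 = 3 to 10 of P(X1 = x1) × P(X2 ≥ 7 − x1). This gives 0.147 at p = 0.21 and 0.802 at p = 0.41, against the stated 0.15 and 0.8. A search for the smallest expected sample size under those limits also returns 10/2/23/6. The design reproduces.

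**Mean of x/23 given continuation, one pre-chosen arm:** (E[X1 | X1 ≥ 3] + 13p)/23.

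| True p | P(continue) | E[X1 given X1 ≥ 3] | Mean of x/23 | Excess (points) |
|---|---|---|---|---|
| 0.21 | 0.353 | 3.535 | (3.535 + 2.73)/23 = 0.272 | +6.2 |
| 0.30 | 0.617 | 3.908 | (3.908 + 3.90)/23 = 0.339 | +3.9 |
| 0.41 | 0.848 | 4.529 | (4.529 + 5.33)/23 = 0.429 | +1.9 |

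**Better of two equal arms.** Replace X1 by the maximum of two independent Bin(10, p) counts. The means become 0.276, 0.350 and 0.451, an excess of 6.6, 5.0 and 4.1 points.

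**All outcomes, one arm.** Add the stopped arms, reported as X1/10. At p = 0.21, E[X1] = 2.1, of which 0.3526 × 3.535 = 1.246 comes from continuing arms and 0.854 from stopped ones. The overall mean is 0.854/10 + 0.3526 × 0.2724 = 0.181, or 2.9 points too low. The same calculation gives 3.2 points too low at 0.30 and 2.1 at 0.41.

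**Which adjusted estimate goes the right way.** Take 7 responses in 23. The possible splits have X1 = 3, 4, 5, 6, 7, with weights C(10, x) × C(13, 7 − x) = 85800, 60060, 19656, 2730 and 120, total 168366.
- Unbiased given continuation (mean of X2/13 over these weights): (4 × 85800 + 3 × 60060 + 2 × 19656 + 1 × 2730)/(13 × 168366) = 43494/168366 = 25.8%. In the same way 8/23 (34.8%) becomes 31.6% and 10/23 (43.5%) becomes 42.3%.
- Standard unconditional UMVUE (mean of X1/10 over the same weights): 61314/168366 = 36.4%, above the plain 30.4%. Its mean given continuation is E[X1 | X1 ≥ 3]/10 = 0.353 at p = 0.21, further from the truth than 0.272.

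**Sensitivity to first-stage size.** Arms of 8 to 12 patients, with the same cutoff and 13 more, give an excess of 8.0 down to 4.9 points at 0.21 and 3.3 down to 1.0 at 0.41.

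**The case against.** The quoted sentence says what counts as a response. It does not prescribe a phase II point estimate or an interval, and estimators after a two-stage design are often left to an analysis plan. That stands as a limit: an unseen plan may already supply an adjusted figure, and its absence from the article is no fault. What remains is that the stated measure is a plain percentage, the stated final count pools all 23, and the two together give x/23.

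The direction of bias also depends on the conditioning, and response is reported for the phase I part too, so a stopped arm has a rate as well. This stands. Conditioning on continuation is still the relevant frame for the figure set beside 0.21 after phase II, because that figure appears only then.

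The size is modest. An arm with no added effect stops at the first stage about 65% of the time. At the design alternative the excess of 1.9 points is small beside a standard error of about 10 points, √(0.41 × 0.59/23).

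Two stronger readings are tempting. A reader might infer that the 7-of-23 test is invalid. For one pre-chosen arm it is not: the exact error rate is 0.147, within the stated 0.15. What choosing between two arms does to that error rate is a separate matter. A reader might also infer that any 23-patient percentage from this trial is too high, or that x/23 is biased upward without condition. The documents support neither: the excess is an average given continuation, and over all outcomes the sign reverses.

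**Conclusion.** The concern holds as a conditional statement about the estimate, and it is of modest importance because response is a secondary endpoint. Over the protocol's own range of 0.21 to 0.41, x/23 after continuation is too high on average by about 6 falling to 2 points for one pre-chosen arm. For the better of two equal arms it is about 7 falling to 4.

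This assumes exactly 10 first-stage patients, independent responses with a common rate in both stages and, for the two-arm figures, selection on response between two equally effective arms that are both acceptably safe. Variable-length blocks or closure of an arm could change the first-stage size; the range for 8 to 12 patients is given above.

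**What to change.** Keep 7 of 23 as the decision rule. State that x/23 will be accompanied by the response rate in the 13 second-stage patients with its exact binomial interval, whatever the test result. Those 13 are untouched by both the first-stage rule and the choice of arm, so their rate is unbiased given either.

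Optionally add an estimate that is unbiased given passage of stage 1, and say explicitly that it conditions on continuation. It corrects for the first-stage rule but not for choosing the better arm. An instruction to use the UMVUE without that qualification would work against the purpose.

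The cost is about one line of analysis, with no extra patients and no change to the test. The 13-patient interval is wide (4/13 gives about 0.09 to 0.61), and the reported rate may look slightly less favourable. If the analysis plan already provides such an estimate, a cross-reference is enough.

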### Data analysis

The current trial aims to evaluate the safety of the combination treatment of pembrolizumab with SBRT and determine whether the sequence of these therapies matters. The primary endpoint is DLT assessed using CTCAE version 4.0. The SBRT schedule associated with DLT in <20% of patients will be determined based on the incidence of treatment-related adverse events.Response rates will be determined using RECIST v1.1. The null hypothesis that the true response rate is 0.21 [10] will be tested against a one-sided alternative. The null hypothesis will be rejected if seven or more responses are observed in 23 patients.Survival times are defined from the day of randomization until progression, last follow-up or death. Cases will be censored at last follow up visit if no progression was observed. Multivariate analysis will be performed according to the cox-regression method.For the evaluation of immunological markers, median values between two groups will be compared by the Mann–Whitney U test, between >2 groups with Kruskal–Wallis testing. To compare proportions of categorical variables, the Pearson’s Chi^2^ test or Fisher’s Exact test will be used. To evaluate correlations, Spearman correlation coefficients will be calculated. All statistical analyses will be performed using SPSS 24.0 (SPSS Inc, Chicago, IL, USA), a *P* value <0.05 will be considered statistically significant.When missing data occurs, analysis will find place with the available data. Due to the small sample size, no imputing will find place.

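### The response test sets a 12-week response in non-irradiated lesions against a null of 0.21 reported only as an overall response rate, and the article gives no basis for carrying 0.21 or 0.41 over to that endpoint

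*Protocol article*

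**What the plan says.** Under Secondary endpoints, the protocol article defines the RECIST v1.1 response rate in the non-irradiated metastases as "the percentage of subjects achieving either a complete or a partial response at 12 weeks after the start of pembrolizumab". The same section schedules CT every 9 weeks, or sooner if clinically indicated.

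Under Sample size, this rate is evaluated in each arm with a Simon two-stage optimum design: "The null hypothesis that the true response rate is 0.21", with a citation, "will be tested against a one-sided alternative". The stage-1 rule is: "If there are two or fewer responses, the alternative hypothesis will be rejected". Table 2 gives 10 patients at stage 1 and 23 in all; 7 or more responses reject the null. The operating characteristics are given as: "This design yields a type I error rate of 0.15 and power of 0.8 when the true response rate is 0.41". Data analysis repeats the null and the final cut-off.

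The article describes the matching benchmark figure in the abstract, where pembrolizumab "has demonstrated a promising overall response rate of 21.1% in patients with progression or recurrence after platinum-based chemotherapy". The Background section gives a range of 15–26% for PD-1/PD-L1 blockade, also called an overall response rate. Neither place gives an assessment time or limits the lesions counted.

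**The concern.** The null and the count to be compared with it are defined differently. The count stops at week 12 and leaves out the irradiated lesion. The benchmark is labelled overall, without either limit. In the same patients and lesions, a rate fixed at week 12 cannot exceed the rate accumulated over treatment, because a patient who first responds later is a failure in the former and a responder in the latter.

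The alternative has the same problem. It equals the null plus 0.20 (0.41 − 0.21 = 0.20), and no separate 12-week source is given for it. Doubt about the scale of the null therefore carries over to the alternative.

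The fixed cut-offs decide whether an arm is futile at stage 1 and whether the combination is declared active at the end, and the same response rate picks the arm for phase II. If the 12-week rate runs below the overall rate, an active combination is more likely to be dismissed at both steps.

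**Working it through.** **Inputs.** From Sample size and Table 2: n1 = 10, r1 = 2, n = 23 (13 more patients at stage 2), r2 = 6, p0 = 0.21, p1 = 0.41, one-sided. From Secondary endpoints: response at 12 weeks, non-irradiated lesions, CT every 9 weeks. From Trial design: 3-weekly cycles, with SBRT ending 1 day before cycle 1 (called arm A here) or cycle 3 (called arm B).

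**Step 1: reproduce the plan's figures.** With X1 ~ Bin(10, p) and X2 ~ Bin(13, p),

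P(reject | p) = Σ over x = 3 to 10 of P(X1 = x) × P(X2 ≥ 7 − x), and P(stop at stage 1 | p) = P(X1 ≤ 2).

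- At p = 0.21: P(reject) = 0.1466, against the stated 0.15.
- At p = 0.41: P(reject) = 0.8024, against the stated 0.8; P(stop at stage 1) = 0.1517.

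A grid search over designs with n ≤ 35, type I error ≤ 0.15 and power ≥ 0.80 returns exactly this design as the one with the smallest expected sample size under the null (14.6). The calculation is sound.

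**Step 2: vary the rate on the tested endpoint.** Let s be the share of overall responders who are counted as responders at week 12. The documents give no value for s, so the range is an assumption. The same formulas at p = 0.41 × s and p = 0.21 × s give:

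| s | 0.41 × s | Power | Wrong stage-1 stop | 0.21 × s | Type I error |
|---|---|---|---|---|---|
| 1.00 | 0.4100 | 0.802 | 0.152 | 0.2100 | 0.147 |
| 0.95 | 0.3895 | 0.753 | 0.185 | 0.1995 | 0.120 |
| 0.90 | 0.3690 | 0.696 | 0.223 | 0.1890 | 0.096 |
| 0.80 | 0.3280 | 0.561 | 0.312 | 0.1680 | 0.058 |
| 0.70 | 0.2870 | 0.408 | 0.418 | 0.1470 | 0.031 |

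If 5% of overall responders are missed at week 12, about 5 points of power are lost (0.802 − 0.753 = 0.049).

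**Step 3: compare week 12 with the scan schedule.** Counting from the start of pembrolizumab, routine CTs fall at about weeks 9 and 18. None falls at week 12, so only one routine on-treatment scan precedes the landmark. In arm B, cycle 3 is given at about week 6 (2 × 3 weeks) and SBRT ends the day before. The week-9 CT is then about 3 weeks after SBRT (9 − 6), and week 12 is about 6 weeks after it (12 − 6). In arm A, the same points come about 9 and 12 weeks after SBRT. The landmark therefore gives the two sequences unequal time after SBRT, although they are compared on this rate.

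**The case against.** A reader might infer that the stated power of 0.8 is overstated or miscalculated. The documents do not support that. Sample size introduces the rate as that of the combination in non-irradiated metastases and gives power on condition that the true rate is 0.41. Read as a statement about the trial's own endpoint, it is correct. No section says that 0.41 was meant as an any-time rate.

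Other objections also carry weight:

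- That 21.1% was a best response at any time is inferred from the word overall. The cited source is not available to confirm it.
- The net direction is not settled. Leaving out the irradiated lesion could shift the rate either way. Inclusion criteria also admit treatment-naive patients, whereas the benchmark is post-platinum; that effect is not quantified either.
- The definition can be read as response achieved by week 12. A response gained and lost before then would still count. Later responders would remain failures, so the mismatch shrinks but does not disappear.
- Unscheduled earlier scans are allowed, and the detailed assessment table is in a supplementary file that is not shown. It may fix the deciding scan.
- If the 12-week rate is lower under the null as well, the test is conservative, so this mechanism does not produce a false claim of activity.
- Twelve weeks equals four 3-weekly cycles, and an early landmark is a legitimate choice for a go/no-go decision.

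These points limit the claim about size and direction. They do not supply the missing basis for applying 0.21 and 0.41 to this endpoint.

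**Conclusion.** The concern holds as a mismatch of definitions, not as an arithmetic error. The stated type I error and power are correct only if the true 12-week rates in non-irradiated lesions are 0.21 and 0.41, and the article gives no ground for either.

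The possible size is material. Over s from 0.95 to 0.70, power runs from 0.75 to 0.41 and the wrong stage-1 stop from 0.18 to 0.42, while type I error falls from 0.12 to 0.03. This range rests on three assumptions: the benchmark is a rate accumulated over treatment, 0.41 was set on that same scale, and nothing else moves the rate. The documents confirm none of them, so no single corrected power can be given. The scan timing adds a separate reason to revise the definition: week 12 falls on no routine 9-weekly CT, and in arm B the only routine scan before it comes about 3 weeks after SBRT.

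**What to change.** Under Secondary endpoints, Sample size and Data analysis, define the tested endpoint as best objective response (complete or partial, RECIST v1.1, non-irradiated lesions) over a fixed number of scheduled CTs. Use the same number in both arms, and at least the first two. Keep the 12-week rate as a supportive endpoint. Two CTs reach about week 18 (2 × 9), so the endpoint is closer to an overall rate but still truncated; the text should say so and give the reason for 0.21 and 0.41 on it.

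If the 12-week landmark stays, state under Sample size that 0.21 is an overall rate and that power is 0.8 only if the 12-week rate is 0.41, show the sensitivity range above, and name the scan that decides the 12-week response.

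The first option needs a wording change but no extra patients and no scans beyond those scheduled. Its cost is that stage 1 may wait for one more scheduled CT in patients not yet in response. An arm passes the futility rule as soon as its third response is seen, but choosing the better arm still needs the full count in both. The second option costs only a less favourable power statement.
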